### Eligibility Criteria

Individuals will be eligible for the trial if they meet the following inclusion criteria:

• adult (aged 18 years or older or as per Local/Provincial Guidelines)

• documented HIV-1 infection (determined by EIA and Western blot)

• documented HSV-2 seropositivity (determined by ELISA during screening; see below)

• no use of chronic anti-HSV therapy for the past 6 months, and not anticipated to require chronic anti-HSV therapy during the study

• antiretroviral naïve (no more than 14 days of total prior ARV exposure)

• CD4 count within the 400-900 cells/mm^3 ^range (inclusive) on two consecutive occasions, with at least one measurement within 4 weeks of initiating trial

• does not meet recommendations for initiating ARV therapy according to current guidelines[57,58]

Chronic anti-HSV therapy refers to the regular, daily use of medications with anti-HSV activity (such as acyclovir, valacyclovir, famciclovir, ganciclovir, valganciclovir, cidofovir, foscarnet). It does not refer to the episodic use of short courses of these medications for treatment of isolated HSV flares for a few days at a time.

The exclusion criteria for this study are as follows:

• pregnancy or actively planning to become pregnant

• receiving chemotherapy, chronic steroid therapy or other immunomodulatory medications (e.g. interferon, azathioprine, methotrexate, TNF-alpha antagonists, etc.)

• Estimated creatinine clearance < 30 mL/min

• Other medical condition likely to cause death within 24 months

• Enrolled in a therapeutic vaccine or immunotherapy trial

• Enrolled in another trial investigating the impact of another intervention on HIV disease progression

• HIV elite controller (EC), phenotypically defined here as documented duration of HIV infection of ≥5 years, a persistent CD4 cell count ≥500 cells/mm^3^, and a persistent plasma HIV viral load of < 1000 copies/mL in the absence of antiretroviral therapy[3,59-61]

A stringent, empiric definition of the EC phenotype will be used because previous reports have primarily characterized ECs on the basis of genetic and immune markers beyond the means of this study[3,59-61]. The heterogeneity of CD4 counts and viral loads in ECs implies that a more permissive definition may overlap considerably with the general HIV-infected population and risk introducing a selection bias.

### Study setting

The VALIDATE trial will be conducted in industrialized/middle-income country settings. The study will randomize 480 participants, 240 in each arm. Participants will be recruited from sites including clinical research sites of the CIHR Canadian HIV Trials Network (CTN), the Instituto de Pesquisa Clinica Evandro Chagas (IPEC) HIV/AIDS Clinical Research Center of the Oswaldo Cruz Foundation in Rio de Janeiro, Brazil, and the Hospital Fernandez/Fundación Huesped in Buenos Aires, Argentina. The CTN is a nationwide partnership established in 1990 of over 30 clinical trial sites across Canada, including both university-affiliated and community-based HIV clinics, with extensive experience in conducting HIV clinical trials. Both the IPEC Centre in Rio and the Hospital Fernandez and affiliated Fundación Huesped in Buenos Aires are national reference centres for infectious disease research, care and training, and are experienced leaders in international HIV/AIDS clinical trials.

### Treatment Groups

Participants in the intervention group will receive oral valacyclovir 500 mg twice daily, the standard dose used for HSV-2 suppression in HIV-infected individuals[15,62]. Valacyclovir is safe and well tolerated, as evidenced by clinical trials, where side effects have been reported at rates no different from those of placebo, and clinical experience[54,55,63,64]. Individuals in the control arm will receive an odourless placebo tablet identical to valacyclovir in appearance and taste, to be taken twice daily. Use of other anti-HSV medication (including topical acyclovir) during the trial is prohibited, except during treatment of herpes flares (described below).

### Randomization and blinding methods

Randomization is stratified by site in permuted blocks of variable size (4 and 6) using a computer-generated list of random numbers. The CTN created and coordinated the allocation sequence, and randomization is performed through a secure website which ensures allocation concealment. All participants and study personnel (including investigators, research coordinators, data analysts) will be blinded to treatment allocation throughout the trial. Access to the allocation code will be restricted to one study statistician who will not perform the final study analyses.

### Outcome Measures

The primary outcome is the time from baseline until reaching the primary endpoint, a composite of either a CD4 cell count ≤ 350 cells/mm^3 ^measured on two consecutive occasions at least 1 month apart, or initiation of HAART for any reason, whichever occurs first. This endpoint was selected because reaching the treatment threshold for initiating HAART is an important clinical event signifying the need for lifelong therapy. The CD4 count of ≤ 350 cells/mm^3 ^must be confirmed by a second measurement to verify the CD4 count is within the treatment range before initiating therapy. The primary endpoint also includes the initiation of HAART for any reason, since patients who start HAART outside these guidelines are also committed to lifelong therapy. This group may include individuals who choose to start therapy at earlier stages of disease (e.g. because of high viral load set-point), and some who develop HIV-related complications (e.g. tuberculosis) at higher CD4 cell counts, among others. For example, women who initiate HAART during pregnancy primarily for the prevention of mother-to-child transmission of HIV, and hepatitis B co-infected individuals who initiate HAART primarily for the purposes of treating their hepatitis B infection, will also be considered to have met the primary endpoint. It was important not to restrict the primary endpoint to initiation of HAART alone, since some patients may not initiate HAART despite reaching treatment thresholds for reasons including patient anxiety, concerns about adherence, and lack of familiarity with guidelines[65].

HAART initiation guidelines are continuously under evaluation, and HIV treatment guidelines may change. However, a change will not threaten the integrity of the study for a number of reasons. First, guidelines on HAART initiation have recently been revised[6,9]. Recommendations to uniformly increase the treatment threshold above 350 cells/mm^3 ^in both industrialized and middle-income settings based on definitive clinical trial data are not anticipated during the course of the trial. Second, as described above, the primary endpoint of this study is a composite of not only meeting the current CD4 threshold of 350 cells/mm^3^, but also the initiation of HAART for any reason, whichever occurs first. Finally, randomization in this trial will be stratified by site to help account for variation in practice regarding initiation of HAART across sites.

The secondary outcome measures to be compared between the two treatment groups include:

• Annual rate of change in CD4 count, calculated as the slope of participants' CD4 count change/time

• Annual rate of change in the CD4 cell count percentage, calculated as the slope of the participants' CD4 count percentage change over time

• Log_10 _plasma HIV viral load at 12, 24 and 36 months of follow-up

• Treatment-emergent adverse events and laboratory abnormalities (CBC, plasma creatinine)

• Frequency of episodes of symptomatic HSV reactivation at any anatomic site

• Proportion of microbiologically confirmed flares of HSV during the trial that are caused by laboratory-confirmed acyclovir-resistant HSV

• Overall quality of life as measured by the MOS-HIV questionnaire at each 6-monthly time point.

### Duration of Study Participation

Study visits will occur every 3 months over 2 years of participant accrual and 3 years of follow-up. Once enrolled, participants will enter the follow-up period during which they will be treated with either valacyclovir or placebo, and undergo follow-up visits every 3 months. Follow-up for an individual participant will continue until the end of the 5-year study period unless the primary endpoint is reached first. This means that all participants will be followed until the 5-year trial ends, unless they reach a primary endpoint first.

### Safety

Adverse events and serious adverse events will be assessed at each study visit, graded on a 4-point scale (Division of AIDS Table for Grading the Severity of Adult and Pediatric Adverse Events), and assessed for their relationship to the study medication/intervention. The Data Safety Monitoring Committee (DSMC) of the CIHR CTN will be responsible for safety monitoring in this trial, and will also conduct safety analyses based on serious adverse events every 6 months, and ad hoc when necessary. The DSMC consists of clinicians, biostatisticians and a community member, from Canada and the United States.

### Adherence Assessments

Adherence will be assessed at each visit through pill counts and through a self-report questionnaire (modified from the ACTG Adherence Questionnaire) at each visit[66,67]. In addition, urine samples will be collected from all study participants at pre-planned visits, stored at -80°C, and tested for acyclovir by mass spectrometry[68] to obtain overall estimates of adherence or cross over. Testing will be performed at the conclusion of the trial to help maintain blinding.

### Management of symptomatic herpes during the trial

If a clinical reactivation of herpes symptoms occurs during the trial, participants are instructed to continue their study drug, present for clinical assessment, have samples taken to attempt microbiologic confirmation of the diagnosis where resources permit, and consider optional open-label treatment. Although participants in the treatment arm may thus receive a total valacyclovir dose of up to 3 g per day for 5 days, this quantity remains well within the safe therapeutic window of this drug. Of note, the occurrence of herpes flares in a study participant does not in itself unblind the study, because a small proportion of individuals taking chronic suppressive anti-HSV medications can experience herpes reactivations. If HSV resistance is suspected, specimens will be tested for acyclovir resistance using a plaque reduction assay[69].

### Ethical approval

Ethical approval was obtained from the Research Ethics Board of the primary study site, the University Health Network (REB# 09-0587-B), prior to commencement of study activities at any site. Each study site also obtained approval from the local research ethics board prior to initiation of the study at that site. The research is being conducted in accordance with the Declaration of Helsinki.

### Sample Size Calculation

It is hypothesized that suppression of HSV-2 using valacyclovir will increase the time until participants' CD4 counts reach ≤ 350 cells/mm^3 ^or initiate HAART from the expected value of 2 years to 2.75 years (see justification below). Participants will be recruited over 2 years and followed over 3 years. Using a conservative estimate that 25% of the sample will be lost to follow-up on average half way through the 3-year follow-up period, the expected years of follow-up is 0.75 × 3 years + 0.25 × 1.5 years = 2.625 years overall. In order to detect a difference of 0.75 years with a two-sided α = 0.0492 (adjusted for multiple analyses by the method of O'Brien and Fleming)[70] and 80% power in a survival analysis, 240 individuals will be required in each study arm, or 480 participants overall[71].

The expected rate at which HIV disease would progress in HAART-untreated individuals was based on both a retrospective review of patient charts and the published literature. Among 142 patients with at least 3 CD4 counts before starting HAART, with baseline CD4 count > 400 cells/mm^3 ^at the Toronto General Hospital Immunodeficiency Clinic, the median time from first presentation to reaching CD4 ≤ 350 cells/mm^3 ^was 2.0 years ([name], [name]: personal communication). In the subset with higher baseline CD4 counts (> 500 cells/mm^3^), the median time was 2.5 years. Consistent with these findings, a published retrospective observational cohort study of 4268 HIV-infected individuals in the United Kingdom with baseline CD4 counts > 500 cells/mm^3 ^also found the median time to until reaching CD4 counts ≤ 350 cells/mm^3 ^or initiation of antiretroviral therapy was 2.5 years[72]. Both are consistent with the generally accepted rate of CD4 count decline of 50-60 cells/mm^3 ^per year[2,3].

Valacyclovir 500 mg twice daily is estimated to decrease HIV plasma viral load by 0.5 log copies/mL. In previous studies, the magnitude of increase in HIV viral load associated with HSV-2 infection and the reciprocal decrease with valacyclovir 500 mg twice daily therapy was 0.33-0.53 log_10 _copies/mL[18,32,33,41,42]. Further, the impact on HIV viral load was more pronounced with time and in those with higher baseline CD4 counts. The median baseline CD4 counts in these trials were 226 (IQR 145-389) and 446 cells/mm^3 ^(IQR 334-628) respectively[41,42]. Among persons with higher baseline CD4 counts of 400-900 cells/mm^3^, valacyclovir is anticipated to reduce HIV viral load by about 0.5 log_10 _copies/mL. Data from large cohort studies of untreated HIV infection that correlate HIV viral load set-points with rates of CD4 cell decline [2,3] suggest that valacyclovir will attenuate the rate of CD4 count decline by 10 cells/mm^3^/year. Over the 3-5 years of follow-up in this study, the treatment arm is thus expected to experience an overall attenuation in CD4 count decline of 30-50 cells/mm^3^, roughly equivalent to the CD4 count decline seen in 9 months. The sample size calculation is based on a prolongation in the time until CD4 ≤ 350 or HAART initiation from 2 to 2.75 years. The Kaplan-Meier estimates of the proportion of ART-naïve patients who experience a fall in CD4 count to ≤ 350 cells/mm^3 ^or who start HAART in the UK study cited above are consistent with these figures[72].

Nine months is a clinically important difference in the time for HIV-infected patients to delay initiation of lifelong HAART. During this time, patients could avoid the costs, toxicity risks, and resistance risks of ARVs. Because typical HAART regimens can cost $1200 per month compared with only $150 per month for valacyclovir, this strategy could result in an annual net savings of nearly $10000 per patient based on medication costs alone. Further, although the toxicity profile of current ARVs is significantly better than in earlier years of the HIV epidemic, long-term toxicities remain unknown because most of the agents in current use were approved within the last 5-10 years. The ARV resistance risks to be avoided are also considerable; in clinical trials evaluating efavirenz-based HAART regimens, the current 'gold standard' for first-line ARV therapy, 30-70% of the 15-20% patients experiencing virologic failure at one year have evidence of resistance to the NNRTI class of drugs, effectively eliminating the potential for using standard agents in this class thereafter[73-77]. Delaying HAART also provides time for patients to prepare psychologically for starting HAART, which is an important predictor of subsequent adherence[78,79]. Nine months is also the time between 3 quarterly appointments, allowing ample time for clinician and patient to prepare for HAART. Finally, although there is theoretical risk of developing drug-resistant HSV with chronic valacyclovir, this risk is minimal even in immunocompromised patients. Resistance rates have stayed stable at 5-6% despite increasing population exposure to related drugs over 2 decades, perhaps because it imposes a fitness cost on the virus[15,80-83]. Resistant HSV is occasionally seen in advanced HIV patients with persistent lesions despite therapy, not in asymptomatic shedding. For safety, those with frequent recurrences unresponsive to therapy during the trial will have their viral isolates tested for resistance.

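### The 25% loss to follow-up enters the sample size only as a shortened average follow-up; treated as censoring, 240 per arm gives about 77% power (74-80% by loss assumption) rather than the stated 80%

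*Protocol article*

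**What the plan says.** All of the following is in the protocol article.

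- Sample Size Calculation gives the schedule: "Participants will be recruited over 2 years and followed over 3 years".
- It assumes that "25% of the sample will be lost to follow-up on average half way through the 3-year follow-up period", calls this conservative, and turns it into a single number: "the expected years of follow-up is 0.75 × 3 years + 0.25 × 1.5 years = 2.625 years overall". No other allowance for loss is described.
- From this it concludes that, at two-sided α = 0.0492 and with "80% power in a survival analysis, 240 individuals will be required in each study arm, or 480 participants overall", a lengthening from 2 to 2.75 years can be detected. The 2-year control value comes from a chart review in which "the median time from first presentation to reaching CD4 ≤ 350 cells/mm^3 ^was 2.0 years".
- Duration of Study Participation says: "Follow-up for an individual participant will continue until the end of the 5-year study period unless the primary endpoint is reached first". With 2 years of accrual in a 5-year study, planned follow-up is therefore 3 to 5 years, and the effect-size justification uses the same 3-5 years.
- Primary Analysis censors participants without an endpoint at their last CD4 count.

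**The concern.** Power in a time-to-event comparison depends on the number of events. A participant who is lost before the endpoint is censored and adds no event after that date. Shortening everyone's follow-up to a common average does not represent this. It leaves the lost quarter at risk for as long as everyone else, including the extra 0 to 2 years that early enrolees gain from staggered entry.

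If so, the expected events are overstated and the stated 80% is optimistic under the plan's own loss assumption. The expected viral-load effect is described as modest, so a null result is a realistic outcome. It would then be interpreted against a power that the design does not quite have.

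**Working it through.** **Inputs (Sample Size Calculation, Duration of Study Participation).** Medians 2 and 2.75 years; 240 per arm; two-sided α 0.0492 (z = 1.967); 80% power (z = 0.842); 2 years' accrual plus 3 years' follow-up; 25% lost, on average at 1.5 years. Assumed here: exponential times and uniform accrual.

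**Formulas.**
- Hazards: ln2/2 = 0.3466 and ln2/2.75 = 0.2521 per year. Hazard ratio 2/2.75 = 0.727, |ln HR| = 0.3185.
- Events needed (Schoenfeld): 4(1.967 + 0.842)²/0.3185² ≈ 311.
- P(event) with accrual A = 2 and further follow-up F: 1 − [exp(−λF) − exp(−λ(F+2))]/(2λ).
- P(event) by a fixed time T: 1 − exp(−λT).
- Power: Φ(√d × 0.3185/2 − 1.967), where d is the number of events.

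**Step 1: the plan's own figure.** With A = 2 and F = 2.625 for everyone, P(event) is 0.710 and 0.595. Then d = 240 × (0.7096 + 0.5947) = 313, and power = Φ(2.817 − 1.967) = 80.2%. A log-rank simulation gives 80.0%. A fixed 2.625 years per person with these medians does not reproduce it: P(event) 0.597 and 0.484, about 260 events, 72.5% power. So 2.625 years stands in for the 3 years after accrual, for everyone.

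**Step 2: what that implies.** Everyone has 2.625 to 4.625 years available, mean 3.625. The stated loss pattern gives 0.75 × 4 + 0.25 × 1.5 = 3.375.

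**Step 3: loss as censoring, 25% lost at 1.5 years after enrolment.** The retained 75% have F = 3 (P(event) 0.745 and 0.631). The lost 25% can have an event only by 1.5 years (0.405 and 0.315).
- Control: 0.75 × 0.745 + 0.25 × 0.405 = 0.660.
- Valacyclovir: 0.75 × 0.631 + 0.25 × 0.315 = 0.552.
- d = 240 × 1.212 = 291. Power = Φ(2.716 − 1.967) = 77.3% (77.8% by simulation).

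**Step 4: other readings of the loss, all at 240 per arm.**

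| Loss assumption | Events | Power |
|---|---|---|
| No loss, 3-5 years | 330 | 82.3% |
| Full 25% lost event-free, exponential loss (0.13/year) | 270 | 74.2% |
| Full 25% lost event-free, only after accrual closes | 285-287 | 76.5-76.8% |
| 25% lost, uniform over 0-3 years from enrolment | 288 | 76.9% |
| **25% lost at 1.5 years from enrolment** | **291** | **77.3%** |
| 25% lost, uniform over own 3-5 years | 297 | 78.2% |
| 25% lost, halfway through own 3-5 years | 301 | 78.7% |
| 25% lost at 1.5 years after accrual closes | 310 | 79.8% |

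Except in the no-loss row and the two marked event-free, the 25% includes people who had already reached the endpoint.

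**Step 5: detectable delay.** Solving the power formula for the treated median at 80% power gives 2.82 years under the 74.2% row, a delay of about 0.8 years instead of 0.75. The milder rows lie in between.

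**Step 6: where the gap comes from.** On a fixed 3-year schedule for everyone, averaging gives 72.5% and censoring the lost at 1.5 years gives 71.8%, a difference of 0.7 points. Most of the overstatement therefore comes from giving lost participants the staggered-entry time, not from averaging as such.

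**The case against.** **The loss could fall after accrual.** The text separates recruitment over 2 years from follow-up over 3 years and places loss within a 3-year period. As individual follow-up is 3-5 years, that period could be the post-accrual phase, which gives 79.8%. This stands as a possible reading. However, Duration of Study Participation starts the follow-up period at enrolment, and this reading needs nobody to be lost during the 2 accrual years.

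**A stronger reading is tempting.** A reader might infer that the figures contradict each other: 313 events plus 120 lost (25% of 480) leaves only 47 (10%) completing event-free, whereas the medians leave 31% event-free with nobody lost (1 − 330/480). That treats the lost and those with events as separate people. The document does not say that the 25% are all lost before an endpoint. If an assumed loss rate includes people who already had the endpoint, the groups overlap and nothing conflicts. For the same reason 74% is the strict end of the range, not the headline.

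**The model is assumed.** The article does not state exponential times. With a Weibull shape of 1.1 (an assumption) and the same medians, loss at 1.5 years gives about 85% power. The hazard ratio then becomes 0.727^1.1 = 0.704, which would lift the plan's own route as well, so this does not rescue the averaging step. If 2 and 2.75 years were means, a fixed 2.625 years would need 232-236 per arm, close to 240, and power with actual loss would be about 80-84%. The text does speak of an expected value, but the control figure is derived from a median, so the median reading is the better supported one.

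**The shortfall is small.** It is 2 to 3 points on the literal reading, and the plan calls its 25% conservative. That limits the importance of the point, but it does not make the stated power correct under the stated loss.

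**Conclusion.** The point holds in a limited form. The arithmetic of 2.625 years is correct, and 240 per arm does follow from it. The error is in what the number is used for: it leaves lost participants at risk for 2.625 to 4.625 years, although the plan has them leaving at 1.5 years on average and censors them at their last CD4 count.

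On the literal reading the stated power is about 3 points too high: 77% with 291 events, against about 311 needed. The range is 74% to 80%, depending on when losses occur and whether the 25% counts only event-free losses. The documents do not support a flat statement that power is 74-77%. Nor do they support blaming averaging alone, which costs under 1 point on a fixed schedule.

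The figures rest on exponential times, uniform accrual and the reading of 2 and 2.75 years as medians.

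**What to change.** In Sample Size Calculation:

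1. Replace the averaged 2.625 years with a calculation that treats loss as censoring within the 3-5 years of follow-up.
2. State whether the 25% means losses before any endpoint, and whether the 1.5 years runs from enrolment.
3. Restate the result: 240 per arm gives about 77% power for 2 versus 2.75 years (range 74-80% by loss assumption), or 80% power for a delay slightly above 0.75 years (up to about 0.8).
4. Name the survival distribution and accrual pattern assumed.

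This is a few sentences of text. Enrolment, analysis and conduct are unchanged. The cost is a slightly less favourable stated power.

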These results bolster interest in the VALIDATE trial, which is addressing related but complementary issues. First, given the conduct of the Partners trial in resource-limited settings, it remains important to study the impact of HSV-2 suppression in co-infected patients from industrialized and middle-income countries. The endpoint of the Partners trial represented a stage of disease that can be avoided in settings where the standard of care is to offer HAART earlier; it is encouraging, therefore, that an exploratory analysis from the Partners trial demonstrated a delay in achieving CD4 < 350 cells/mm^3 ^from acyclovir as well (HR = 0.81, 95%CI 0.71-0.93, p = 0.002). Further, rates of CD4 count decline may be different in Sub-Saharan Africa due to the effects of nutritional status, heightened levels of immune activation (for example, as a result of co- or intercurrent infections), and HIV clade[46-49]. The predominant clades in Sub-Saharan Africa (A, D and C) differ from those in most industrialized countries (B and some others) and in South America (B but some F, C and recombinants)[50,51]. In addition, it should be noted that disease progression was a secondary endpoint of the Partners trial, which was primarily designed to study the impact of HSV-2 suppression on HIV transmission. Finally, VALIDATE is employing valacyclovir instead of acyclovir for HSV-2 suppression, and the dose of 500 mg twice daily has been demonstrated to achieve excellent herpes suppression in clinical trials of HIV, HSV-2 co-infected adults[41,42]. Valacyclovir is the pro-drug of acyclovir, and may offer advantages over acyclovir owing to an improved bioavailability (54.5% versus 15-30%) and lower pill burden[52].

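### The expected slowing of CD4 decline by 10 cells/mm³/year implies a delay of 0.4–0.5 years, not the 0.75 years on which the trial is powered

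*Protocol article*

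**What the plan says.** All of the following is in the protocol article.

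- **Target.** Sample Size Calculation takes the time to CD4 ≤ 350 or HAART to lengthen "from the expected value of 2 years to 2.75 years". With a "two-sided α = 0.0492" it requires "80% power in a survival analysis, 240 individuals will be required in each study arm, or 480 participants overall".
- **Follow-up.** "Participants will be recruited over 2 years and followed over 3 years". It assumes "25% of the sample will be lost to follow-up on average half way through the 3-year follow-up period", which it converts to 2.625 years of expected follow-up.
- **Untreated course.** A clinic chart review gives a median of 2.0 years to CD4 ≤ 350. This is described as consistent with "the generally accepted rate of CD4 count decline of 50-60" cells/mm³ per year.
- **Derivation of the effect.** A viral load reduction of about 0.5 log is said to slow CD4 decline by 10 cells/mm³/year. Over 3–5 years this becomes an "overall attenuation in CD4 count decline of 30-50 cells/mm^3^, roughly equivalent to the CD4 count decline seen in 9 months". The next sentence bases the sample size on a move from 2 to 2.75 years.
- **Clinical importance.** The same section then argues separately that nine months is a worthwhile delay.
- **Outside evidence.** Background quotes, for CD4 < 350 in an earlier acyclovir trial in Sub-Saharan Africa, "HR = 0.81, 95%CI 0.71-0.93, p = 0.002".

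**The concern.** The saving is accumulated over one period and spent in another. Thirty to fifty cells is what a slowing of 10 cells/mm³/year yields by years 3 to 5. The event to be delayed is expected at year 2. The slope figures and the target delay, which the text presents as cause and consequence, therefore do not agree.

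The 80% power belongs to the larger delay. A reader who follows the justification will take it as the chance of detecting valacyclovir working as the article expects. If that chance is well below 80%, a non-significant result says less about the mechanism than the section implies.

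**Working it through.** **1. The plan's own figure.** Under constant hazards, HR = 2/2.75 = 0.727 and ln HR = −0.318. Events needed = 4(z₁ + z₂)²/(ln HR)², with z₁ = 1.967 (two-sided α 0.0492) and z₂ = 0.842 (80% power). This gives 4 × 2.808²/0.318² ≈ 311. Two set-ups reproduce 480:

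- **A.** Read 2 and 2.75 years as medians, with 2 years of uniform accrual and a further 2.625 years of follow-up. Event probabilities are 0.710 and 0.595, mean 0.652; 480 × 0.652 = 313 events; power 80.2%.
- **B.** Read them as exponential means, with 75% followed for 3 years and 25% for 1.5 years. Event probabilities are 0.715 and 0.603, mean 0.659; 480 × 0.659 = 316 events; power 80.6%.

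So 480 is right for 2 to 2.75 years.

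**2. Delay implied by the slope effect.** Let d be the untreated decline per year, taken as linear. A control participant who reaches 350 at 2 years has lost 2d cells. Under treatment the same loss takes 2d/(d − 10) years.

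| d | Cells lost by 2 years | Treated rate | Treated time | Delay | Time ratio | HR (constant hazard) |
|---|---|---|---|---|---|---|
| 50 | 100 | 40 | 2.50 y | 0.50 y | 1.25 | 0.80 |
| 55 | 110 | 45 | 2.44 y | 0.44 y | 1.22 | 0.82 |
| 60 | 120 | 50 | 2.40 y | 0.40 y | 1.20 | 0.83 |

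The planned time ratio is 2.75/2 = 1.375. The implied ratio d/(d − 10) does not depend on the baseline CD4 count.

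**3. What 0.75 years would need.**

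- Slowing needed from a 2-year control time: d(1 − 2/2.75) = 13.6 (d = 50) to 16.4 (d = 60) cells/mm³/year.
- Control time needed with a slowing of 10: 0.75(d − 10)/10 = 3.0 to 3.75 years, not 2.
- With the 2.5-year median quoted for baseline CD4 > 500, the delay is 2.5 × 10/(d − 10) = 0.63 to 0.50 years, still short of 0.75.

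**4. Power at 480 for the slope-based effect.** Power = Φ(√(D/4)·|ln HR| − 1.967), where D is the expected number of events.

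| Treated time | HR | D (A / B) | Power (A / B) | Events for 80% |
|---|---|---|---|---|
| 2.75 y (planned) | 0.727 | 313 / 316 | 80.2% / 80.6% | 311 |
| 2.50 y | 0.80 | 321 / 324 | 51% / 52% | 634 |
| 2.40 y | 0.833 | 325 / 328 | 37% / 38% | 949 |

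Example (A, 2.5 years): √(321/4) × 0.223 = 2.00; 2.00 − 1.967 = 0.033; Φ(0.033) = 0.51.

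**5. Sensitivity to hazard shape.** The shapes here are assumptions, since the article gives none. Under set-up A with Weibull times, shape 1.25 gives 56% (2.4 y) to 73% (2.5 y), and shape 1.5 gives 74% to 89%. The same shapes give 95% and 99% for 2.75 years, so they do not reproduce the stated 80%.

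**6. What a null result would leave open.** With about 325 events, the standard error of ln HR is about 2/√325 = 0.111. An estimated HR of 1.00 would have an interval of exp(±1.967 × 0.111), about 0.80 to 1.24. That still contains 0.83 and reaches almost to 0.80.

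**The case against.** - **The quoted sentence is fair as an approximation.** At 50–60 cells/mm³/year, 30–50 cells is 30/60 = 0.5 to 50/50 = 1.0 years of decline, and the midpoint 40/55 = 0.73 years is 8.7 months. This stands. The fault is the next step, which applies those months at year 2.
- **The 80% is attached to 0.75 years, and nine months is defended on clinical grounds.** Both are true. A reader might infer that the sample size calculation is wrong, but it reproduces. A clinically important difference is a legitimate target. What fails is presenting it as the expected consequence of a slowing of 10 cells/mm³/year.
- **The power figures depend on the model.** This also stands. Decline towards a threshold tends to give rising hazards, and power would then be higher (working, step 5). HAART starts unrelated to CD4 slope also count as endpoints; the slope argument gives no reason for those to be delayed, and they could pull power the other way. Constant hazards are used because they reproduce 480. The 0.4–0.5 year result needs only linear decline.
- **The UK cohort is cited in support.** The article says its Kaplan–Meier estimates are consistent with these figures but gives no estimates that bear on the treatment effect. Its quoted median is for baseline CD4 > 500.
- **Still lower power might be inferred.** Medians with a flat 2.625 years and no accrual term would lower it further, but that set-up gives only 72.5% even for 2.75 years, so it is not the plan's basis. Scaling the slope effect down to the lower end of the viral load range is not supported either: the article argues for about 0.5 log and gives no slope for smaller reductions.

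**Conclusion.** The point holds as an inconsistency within Sample Size Calculation. The article's own inputs give a move from 2 to 2.4–2.5 years, which is 53–67% of the stated delay (0.40/0.75 to 0.50/0.75). Nothing elsewhere in the document repairs the step. This rests on linear CD4 decline and the quoted 2 years, 50–60 and 10 cells/mm³/year.

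Under the constant-hazard set-ups that reproduce 480, power for that effect is about 37–52%. This second figure is conditional on the hazard shape and should be reported as such.

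The acyclovir trial's hazard ratio of 0.81 falls within the implied 0.80–0.83, but it is context only. It comes from an exploratory analysis with a different drug and population, and its interval of 0.71–0.93 also contains the planned 0.727. Nor does the finding show that 480 is too few for the stated target, or that the trial must enlarge.

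**What to change.** In Sample Size Calculation:

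1. Correct the justification: a slowing of 10 cells/mm³/year, against 50–60 and a 2-year control time, implies 2 to 2.4–2.5 years.
2. Present 0.75 years as the clinically important difference that 480 participants can detect with 80% power, not as the expected effect. Note that it corresponds to a slowing of about 14–16 cells/mm³/year.
3. State that power for the slope-based effect (HR about 0.80–0.83) is about 37–52% under exponential times, and would be higher if hazards rise over time.
4. State that a non-significant result cannot by itself exclude that effect and will be interpreted from the confidence interval for the hazard ratio.

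The cost is a rewritten paragraph and a less favourable power statement for the expected effect. Enrolment, endpoint, significance level and primary analysis stay as they are.
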